***The available information suggests that the present study has a favorable risk-benefit ratio.***

## **2 STUDY OBJECTIVES**

### **2.1 Primary Objective**

To determine whether injection of autologously-derived bone marrow stem cells yields a functional benefit in addition to the coronary artery bypass graft (CABG) operation as determined by left ventricular heart function (LVEF-MRI).

### **2.2 Secondary Objectives**

To determine the effects of an injection of autologously derived bone marrow stem cells on physical exercise capacity, cardiac function, safety and Quality of Life (QoL).

### 3 OVERALL DESIGN AND PLAN OF THE STUDY

#### 3.1 Overview

This will be a placebo controlled, prospective, randomized, double-blind multicenter, phase III, clinical trial investigating the effects of intramyocardial injection of 5 mL CD133+ bone marrow cells or placebo in 142 patients with coronary artery disease scheduled for CABG surgery. Patients will be randomized to one of the two treatment groups (CD133+ or placebo) in a 1:1 ratio.

Patients will be required to attend 7 study assessments:

1. Assessment I prior to the operation (screening)
2. Assessment Ia between day -2 and day of operation (day 0; cell preparation and transfer)
3. Assessment II at day of operation (injection of study treatment)
4. Assessment IIa at day after operation (post OP/ICU)
5. Assessment III during the postoperative stay before or after discharge (within 72 hours of discharge)
6. Assessment IV (by telephone) at 3 months after the operation
7. Assessment V at 6-months after the operation (data closure)

At Assessment I the patient will be asked to sign the informed consent and baseline criteria will be assessed.

At Assessments I, III and V patients will undergo a 6-minute walk test (physical examinations and vital signs), Holter, 12-lead ECG, cardiac magnetic resonance imaging (MRI) and echocardiography, checking of unwanted tissue changes, laboratory including NT-proBNP and New York Heart Association (NYHA) and Canadian Cardiovascular Society (CCS) evaluations as well as listing of concomitant medications.

Adverse events (AE) will be assessed continuously (informed consent to study end). Furthermore, major adverse cardiovascular events (MACE) will be assessed at Assessment V. At Assessment IIa patients will undergo laboratory and 12-lead ECG evaluations at ICU.

At Assessments I, IV and V patients will be asked to complete QoL questionnaires.

Assessment Ia is related to cell-preparation and transfer and Assessment II is related to injections of study treatment.

The planned patient recruitment is 5 years, the planned duration of study, including follow-up (6 months) is 5.5 years. The duration of the study for each patient will be approximately 6 months.

An obligatory safety follow up is planned for further 18 months after study data closure. Therefore the patients will be required to attend 24 months after the operation Assessment VI. This will be outside the study after data closure. At Assessment VI patient will undergo examination of all safety parameters and will be asked to complete QoL questionnaires. AE documentation and reporting for the safety follow-up will include all (possibly) related AEs and all AEs of specific interest including MACE and death.

The trial will be conducted at seven sites in Germany. Patients will be informed by the study physician and guided additionally through the whole study by a "Study Pass".

A Safety Monitoring Board (SMB) will be responsible for the overall safety of the patients in the trial. See Section 9.9 for further details.

Discontinuation criteria for patients, for parts of the study, and the entire study are described in Section 4.3.

See Appendix 1 for the trial flow chart and Table 2 for the schedule of trial assessments.

In all cases retention of samples of bone marrow and stem cells are stored for safety reasons in the laboratory up to the end of the study. After the end of the study (approx. 2.5 years) the patient may decide what should happen to the stored material: The patient may donate the samples for a research study (pseudonymous) or decide for a further storage or for the destruction of the material. Therefore, all patients will be unblinded at the end of the study and will decide on the use of the material.

During the preparation procedure a small fraction of the cells will be used for research-related investigations (project: “Weitere funktionelle Analysen von adulten Knochenmark-Stammzellen in vitro und in vivo”). The patient agrees to the procedure by a signature on the informed consent form.

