#### Safety Parameters

1. Recording of AEs
2. MACE (cardiac death, myocardial infarction, secondary intervention/reoperation, ventricular arrhythmia) and tachycardial supraventricular arrhythmia  $>160$  bpm (Holter ECG).
3. Laboratory tests (post-operative check and specific tests for cell preparation)
4. Unwanted tissue changes (tumors) will be monitored by MRI and/or echocardiography
5. Vital signs (blood pressure and pulse)
6. Physical examination, 12-lead ECG

Safety parameters will be determined during the 7 study assessments.

An obligatory 2 years follow up will be conducted 18 months after data closure of the study (Assessment VI).

At Assessment VI (after finalization of the study) patients will undergo:

1. Recording of AEs
2. MACE (cardiac death, myocardial infarction, secondary intervention/reoperation, ventricular arrhythmia) and tachycardial supraventricular arrhythmia  $>160$  bpm (Holter ECG).

3. Laboratory tests
4. Unwanted tissue changes (tumors) will be monitored by echocardiography
5. Vital signs (blood pressure and pulse)
6. Physical examination, 12-lead ECG
7. QoL-Score

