| Randomization to treatment                     |                 | X                          |                |                 |                                    |                                     |                              |                                     |
| Cell/placebo preparation                       |                 | X                          |                |                 |                                    |                                     |                              |                                     |
| Cell/placebo transfer                          |                 | X                          |                |                 |                                    |                                     |                              |                                     |
| Injections of study treatment/ CABG            |                 |                            | X              |                 |                                    |                                     |                              |                                     |
| MACE                                           |                 |                            |                |                 |                                    |                                     | X                            | X                                   |
| Concomitant medications                        | X               | X                          | X f | X               | X                                  | X                                   | X                            | X                                   |
| Adverse events/Serious Adverse Events          | X               | X                          | X              | X               | X                                  | X                                   | X                            | X                                   |

a = SF 36 & MLHF-Q, EQ-5D; b = 36 hours after OP; after 0, 6, 12, 24 hours only CK, CK-MB, TNT. c = For female patients of childbearing potential only, d = 18 months after study finalization, e = patients receive dates for follow-ups, f = surgery standard medication will not be documented, g = only for patients with known hypersensitivity or sensitization against murine products;

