#### 7.2.6.2 *6-Month Follow-Up post OP ( $\pm 2$ weeks, Assessment V)/Early Termination*

- Study termination
  - has the study been terminated according to protocol? If yes, proceed with Physical examination/vital signs
  - If study was early terminated:
    - Date of withdrawal/early termination
    - Reason for withdrawal/early termination (AE, at the discretion of the investigator, violation of eligibility criteria, deviation from the treatment plan specified in the protocol, pregnancy, patient withdraws consent, death, other (describe))
- Date of patient contact
- Vital signs (see Section 6.3.2.2)
- General physical examination (see Section 6.3.2.3)
- Blood sampling for laboratory tests (Hematology, Clinical Chemistry and Electrolytes; see Section 6.3.2.1)
- Blood sampling for NT-proBNP (pg/mL; to be sent to Core Lab; see Section 6.3.2.1)
- Cardiac MRI scan and echocardiography to be sent to Core Lab (see Sections 6.1.1 & 6.1.2, 6.1.5 & 6.1.6)
- Classification of heart failure with NYHA and angina with CCS (see Section 6.1.3)
- Holter and LOWN classification (historic data may be used, see Section 6.3.2.4)
- 12-lead ECG (see Section 6.3.2.5)
- Determination of MACE (see Section 6.3.1.6)
- Completion of QoL questionnaires (MLHF and SF-36; see Section 6.2.)
- 6-Minute Walk Test (6MWT, see Section 6.1.7)
- Documentation of any change in concomitant medication
- Documentation of any AE/SAE since last assessment

*7.2.6.3 24-Month Follow-Up post OP ( $\pm$  2 weeks, Assessment VI after data closure for safety reason)*

- Date of patient contact
- Vital signs (see Section 6.3.2.2)
- General physical examination (see Section 6.3.2.3)
- Echocardiography from practice based cardiologist (see Sections 6.1.1, 6.1.2, & 6.1.6)
- Holter from practicing cardiologist and LOWN classification (see Section 6.3.2.4)
- Blood sampling for laboratory tests (Hematology, Clinical Chemistry and Electrolytes; see Section 6.3.2.1)
- Blood sampling for NT-proBNP (pg/mL; to be sent to Core Lab; see Section 6.3.2.1)
- Completion of QoL questionnaires (MLHF and SF-36; see Section 6.2.)
- Performance of 12-lead ECG (see Section 6.3.2.5)
- Determination of MACE (see Section 6.3.1.6)
- Documentation of concomitant medication related to treatment of AE/SAE

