## 8 STATISTICAL METHODS

Before unblinding, a separate statistical analysis plan (SAP) will be finalized, providing detailed methods for the analyses outlined below. Analyses will be performed after database lock.

Any deviations from the planned analyses will be described and justified in the final integrated study report.

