### **8.6 Safety Analyses**

Adverse events (AEs) and serious adverse events (SAE) (comp. Sections 6.3), will be listed summed by occurrence, severity (comp. Section 6.3.1.2.1), outcome, and causal relationship to treatment (comp. Section 6.3.1.2.2) and will be descriptively compared between the two treatment groups using Fishers exact test. Associated AE tables present the total number of patients reporting at least one specific event and the maximum severity grade (patients reporting more than one episode of the same event are counted only once by the maximum severity and highest causality). Special tables will be displayed for MACE (comp. Section 6.3.1.6) and for AEs leading to withdrawal.

In addition, summary tables with patient identification will be presented. The tables provide the numbers and percents of patients with AEs, and also include the subject identification in the table.

Separate summarizations of AEs by worst severity, and of SAEs and AEs that are likely related to treatment and AEs that are unlikely related to treatment (comp. Section 6.3.1.2.2) will also be provided. All AEs will be listed.

Descriptive statistics for laboratory parameters (comp. Table 1, Section 6.3.2.1) will be presented by treatment group and time point. For continuous laboratory parameters, changes from baseline to the other time points will be presented by treatment group and descriptive statistics will be calculated.

Values will also be presented according to the CTC categories. Values outside corresponding normal ranges will be displayed and tabulated.

A new abnormality is defined as an out-of-range value that was previously normal or a value that is initially out of range in one direction (either low or high) and becomes out-of-range in the opposite direction at the end of the period. A worsened abnormality is a value that was out of range at the start and became more abnormal during the period. Should the rate of new or worsened abnormalities be deemed excessive, further examination of the nature of the abnormalities will be performed.

Changes in vital signs (comp. Section 6.3.2.2) and electrocardiograms will also be examined for treatment group differences.

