### 9.10 Duration of the Study

For an individual patient, the maximum duration of the study for each patient will be approximately 6 months (including up to 7 days for screening, 1 day of treatment and up to 6 months follow-up).

The study will close when all patients have completed the 6-Month Follow-up Assessment (Assessment V).

A safety follow-up will be performed 24 months after OP (Assessment VI).

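### The protocol contradicts itself on whether the obligatory month-24 safety data belong to the trial, assigns them no database lock, and does not secure blinding until that visit

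*Protocol*

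**What the plan says.** **Status of the visit.** Assessment VI is obligatory. Section 3.1 states: "This will be outside the study after data closure". The synopsis (Design) and section 6.3.2 repeat this. The synopsis (Safety Parameters) has: "At Assessment VI (after finalization of the study) patients will undergo". A footnote to Table 2 dates the visit "18 months after study finalization", and the title of section 7.2.6.3 has "Assessment VI after data closure for safety reason".

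**Closure and lock.** Section 3.1 lists "Assessment V at 6-months after the operation (data closure"). Section 9.10 states: "The study will close when all patients have completed the 6-Month Follow-up Assessment (Assessment V"). Section 8 says only: "Analyses will be performed after database lock". Apart from the interim analysis, no other data cut is described.

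**Safety analysis.** Under section 8.6, adverse events "will be descriptively compared between the two treatment groups using Fishers exact test". No time limit is given. The MACE tables refer to section 6.3.1.6, which assesses MACE at month 6 and at the 24-month follow-up.

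**Unblinding.** Section 3.1 unblinds all patients at the end of the study so that they can decide about stored samples, and attaches a figure of about 2.5 years to that decision. Section 5.4 breaks the overall code for reporting once the final clinical data are entered and queried. It does not say whether Assessment VI data count as final.

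**Collection after month 6.** Section 3.1 keeps related events, events of specific interest including MACE, and deaths. Section 6.3.1.5 drops other events unless they are judged at least possibly related or are fatal.

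**The concern.** Section 1.3 names tumour formation, unwanted tissue formation and ventricular arrhythmia among the potential risks, and section 2.2 makes safety a secondary objective. The month-24 visit exists to look for late harm, and late harm can be attributed to the cells only by comparing the randomised arms. If the data are outside the study, nobody is bound to make that comparison. If they are inside, the only lock described comes before some of them exist.

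Blinding matters at this visit for two kinds of data. One is the events that are documented only if someone judges them related. The other is quality of life, which patients report themselves. Either could shift if the patient or the assessor knows the allocation.

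**Working it through.** **1. Denominator.** Section 8.7 plans 60 evaluable patients per group (difference 4.5, SD 7.5, two-sided 5%, 90% power). A two-sample t test with the non-central t distribution gives power 0.898 at 59 and 0.903 at 60 per group, so 60 reproduces. With 15% drop-out, 60 / 0.85 = 70.6, so 71 per group and 142 in total, as stated.

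**2. Do month 6-24 data belong to the by-arm analysis?**
- Against: sections 3.1 and 6.3.2, the synopsis, Table 2 and section 7.2.6.3 all place the visit after closure. The synopsis says that safety parameters are determined during the seven study assessments, which do not include VI.
- For: section 8.6 has no time limit and refers to sections 6.3 and 6.3.1.6. Section 6.3.1.5 follows events of specific interest to Assessment VI. The synopsis (Design) lists MACE at V and VI, although section 3.1 lists it at V only.

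The document supports both answers and chooses neither.

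**3. Who reaches Assessment VI after closure?** Section 3.1 gives 5 years of recruitment and 5.5 years in total. A patient operated on at time s (years) has Assessment VI at s + 2. This falls after closure if s + 2 > 5.5, that is, if s > 3.5. The accrual pattern is not given, so it is assumed:
- Uniform: (5 − 3.5) / 5 = 0.30, and 0.30 × 142 = 42.6, about 43 patients.
- Linearly falling: (1.5 / 5)² = 0.09, about 13 patients.
- Linearly rising: 1 − (3.5 / 5)² = 0.51, about 72 patients.

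If uniform recruitment took 3 or 7 years instead, the share would be 1.5 / 3 = 50% or 1.5 / 7 = 21%.

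**4. Follow-up time missed** (142 patients, no deaths or losses). Planned: 142 × 2 = 284 patient-years.
- Single lock at closure, uniform accrual, counting only time not yet elapsed: the late group lacks 0.75 years on average, so 42.6 × 0.75 = 32 (11%).
- Same lock, but the late group loses all of months 6-24 because its visit has not happened: 42.6 × 1.5 = 64 (22.5%).
- Tables cut at each patient's month 6: 142 × 1.5 = 213 (75%). This is a worst case that section 8.6 does not state.

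**5. When are patients unblinded?**
- At closure as defined in section 9.10: year 5.5, before Assessment VI for the late group in step 3.
- 2.5 years from each operation: month 30, later than month 24, so nobody is unblinded early.
- 2.5 years after closure: 5.5 + 2.5 = year 8.0, later than the last Assessment VI at 5 + 2 = 7.0, so nobody is unblinded early.

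The sentence that orders the unblinding carries no figure of its own. It says only that it happens at the end of the study, and section 9.10 is the one place that defines when the study closes.

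**The case against.** A reader might infer that all month 6-24 safety data are excluded from the comparison, so that 75% of planned patient-time is never compared between arms. The documents do not support this. No sentence excludes the data, section 8.6 sets no horizon, and its MACE reference reaches month 24. Under uniform accrual, 70% of patients would have passed month 24 by closure.

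A reader might also infer that patients will be unblinded before Assessment VI. Again the text does not go that far. Both ways of counting the 2.5 years in step 5 put unblinding after the visit, and the overall code break in section 5.4 is for reporting, not for disclosure to patients or sites.

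Nor do the main late risks hinge on judged relatedness. Deaths, MACE and events of specific interest are documented regardless; ventricular arrhythmia is on the Appendix 2 list, and unwanted tissue changes are checked by echocardiography at Assessment VI. Section 7.2.6.3 even asks for any adverse event to be documented at that visit, which sits uneasily with the restriction in section 6.3.1.5.

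Finally, details of a month-24 analysis could be in the statistical analysis plan, and separating long-term safety from the main lock is a legitimate choice.

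These points limit the finding but do not remove it. The status of the visit, the closure of the study and the time of unblinding are fixed in the protocol itself, and they conflict there. An analysis plan cannot settle when patients and sites are unblinded, and neither reading of the 2.5 years agrees with section 9.10.

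**Conclusion.** The point holds as a contradictory rule, not as a proven loss of data. The protocol does not settle whether month 6-24 safety data are part of the by-arm analysis and assigns them no lock. With a lock at study closure, about 43 of 142 patients (30%) would have their month-24 data missed. This assumes uniform accrual over the planned 5 years; linearly falling or rising accrual gives 9% to 51%.

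The same patients could be unblinded before Assessment VI if the study's end means what section 9.10 says, and none would be if the 2.5 years runs from each operation. The exposure is confined to adverse events that are neither fatal, nor MACE, nor of specific interest, and to patient-reported quality of life.

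The month-6 primary endpoint is untouched. The sponsor should make the correction, because a 24-month safety visit is of limited use without a stated comparison and secured blinding. Confidence is medium, given the ambiguity of the 2.5 years and the assumed accrual.

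**What to change.** - **Sections 3.1, 8.6 and 9.10:** define Assessment VI data as a second, separately locked safety cut of the same trial. Compare it descriptively by randomised arm in an addendum to the study report. Include deaths and MACE to month 24, events of specific interest, related events, unwanted tissue changes and Holter findings.
- **Section 3.1:** replace unblinding at the end of the study with unblinding after each patient's own Assessment VI, and remove or define the 2.5 years.
- **Section 5.4:** state that patients and site assessors stay blinded until that point, and limit the code break at the month-6 lock to the analysis team.

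The month-6 efficacy lock does not change. The cost is protocol wording, one further lock and an addendum, all using data already collected, with no new visits or procedures. The downsides are a later final safety report and, for some patients, a later decision on their stored samples.

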#### *6.3.1.5 Adverse Events of Specific Interest*

Events that are listed in Appendix 2 are considered to be of specific interest for the purpose of this study and are monitored in detail. Documentation and reporting of Adverse Events of Specific Interest will be according to the standard procedure of SAE reporting in Section 6.3.1.3.2. continuously up to study end and furthermore as safety follow up to Assessment VI after 24 months. After study termination (Assessment V, 6-Month Follow-Up) AEs not listed as AEs of specific interest will not be documented unless they are possibly, probably or definitely related to the investigational medicinal product or result in death. In case of seriousness all possibly, probably or definitely related AEs will be reported at Assessment VI, 24-Month Follow-Up.

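### Section 3.1 unblinds every patient at an end of study that is not defined in one way, so some patients could learn their arm before the 24-month assessment

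*Protocol*

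**What the plan says.** Section 3.1 explains that bone marrow and stem cell samples are kept in the laboratory and that the patient later chooses their fate: "After the end of the study (approx. 2.5 years) the patient may decide what should happen to the stored material". The next step is a rule for every patient: "Therefore, all patients will be unblinded at the end of the study and will decide on the use of the material".

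The end of the study is described in several ways:

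- Section 9.10 gives the formal closing rule, at trial level: "The study will close when all patients have completed the 6-Month Follow-up Assessment (Assessment V"). Section 3.1 puts this on the calendar: "The planned patient recruitment is 5 years, the planned duration of study, including follow-up (6 months) is 5.5 years".
- Section 3.1 also gives a duration per patient: "The duration of the study for each patient will be approximately 6 months".
- Section 6.3.1.5 equates study termination with the month-6 visit. Footnote d of Table 2 places the 24-month visit 18 months after finalization of the study, which again points to month 6.
- The synopsis introduces the last visit with: "At Assessment VI (after finalization of the study) patients will undergo". Section 3.1 likewise places it outside the study.

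Assessment VI collects all safety parameters and the quality-of-life questionnaires (Section 3.1), and MACE (Section 6.3.1.6). Section 5.4 allows the overall code to be broken only for reporting, once the final clinical data are in, queries are resolved and patients are assigned to analysis populations. No section says that patients or sites stay blinded until Assessment VI.

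**The concern.** The unblinding rule depends on a term that the protocol does not use in one sense, and on some readings allocation is disclosed before the 24-month visit. That visit is the only scheduled one after month 6, so it carries whatever long-term randomised comparison of safety and quality of life the trial can offer.

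Three kinds of data would be exposed for a patient who already knows the arm:

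- Quality of life is self-reported and open to expectation.
- Reintervention, a component of MACE, partly reflects decisions by patients and doctors.
- Relatedness of adverse events is a judgement, and it decides what is recorded. Section 6.3.1.5 says: "After study termination (Assessment V, 6-Month Follow-Up) AEs not listed as AEs of specific interest will not be documented". It excepts fatal events and those judged at least possibly due to the product. An event in someone known to have had placebo is less likely to be called related.

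The last route also requires the assessing physician to know the arm. Section 3.1 mentions only patients; that the site would learn it too is plausible but not stated.

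**Working it through.** **Inputs.** Recruitment 5 years = 60 months; follow-up to Assessment V 6 months; total 5.5 years (Section 3.1). Assessment VI at 24 months ± 2 weeks (Table 2). Planned sample 142 (Section 4.4). Formal close when the last patient completes month 6 (Section 9.10). Assumption not in the protocol: uniform accrual over the 60 months.

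**Reproducing the protocol's figures.** 60 + 6 = 66 months = 5.5 years, as stated. Assessment VI minus Assessment V: 24 − 6 = 18 months, as stated.

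**Share whose Assessment VI falls after the formal close.** A patient operated on at month *u* reaches Assessment VI at *u* + 24. This is later than the close if *u* > 66 − 24 = 42.

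- Uniform accrual: (60 − 42)/60 = 0.30, and 0.30 × 142 = 42.6, about 43 patients.
- With the ± 2-week window (0.5 month): 17.5/60 = 29% to 18.5/60 = 31%, or about 41 to 44 patients.
- Back-loaded accrual, taking cumulative accrual as (t/60)^p: share = 1 − (42/60)^p, which is 41% for p = 1.5, 51% for p = 2 and 66% for p = 3.
- Each month between close and disclosure lowers the uniform-accrual share by 1/60, or 1.7 percentage points (142/60 = 2.4 patients). Section 5.4 requires data entry and query resolution before the code is broken, so 30% applies to disclosure immediately at the close.

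**By reading of the end of the study:**

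| Reading | Share told before Assessment VI |
|---|---|
| Formal close, Section 9.10 | 30% under uniform accrual |
| 2.5 years (30 months) from each operation | 0%, since 30 > 24 |
| 2.5 years after the formal close | 0%: 66 + 30 = 96 months, and the last patient reaches Assessment VI at 60 + 24 = 84 |
| Each patient's own month 6 | 100%, but in conflict with other sections (see the objection) |

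The 2.5 years cannot run from the start of the trial: month 30 falls within the 60-month recruitment period.

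**Adverse events after month 6.** Section 6.3.1.5 limits documentation of events that are neither of specific interest nor fatal to those judged at least possibly related. Section 7.2.6.3, on Assessment VI itself, asks for any AE or SAE to be documented and uses relatedness only to limit reporting. The two sections disagree, so how far recording depends on a relatedness judgement is itself unsettled.

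**The case against.** The strongest defence is the time given beside the rule. The sentence about 2.5 years and the unblinding sentence serve the same decision on stored material. Counted from the operation, 30 months falls after Assessment VI, and nobody is told early. That reading is possible, but the starting point is not given and the figure does not match the formal close. The defence shows an ambiguity; it does not show that the blind is protected.

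A reader might infer the opposite extreme: that the protocol defines the end as each patient's month 6, so that all 24-month data are open-label. The documents do not support this. Section 9.10 closes the study for all patients together. Rolling disclosure would conflict with Section 5.4, which breaks the overall code only for reporting after the data are final and requires an unblinded patient to be withdrawn unless continuation is specifically approved. It would also conflict with Section 7.2.2, under which allocation is entered on the cell preparation form only after the last patient is out.

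A reader might also infer that the 24-month safety comparison is biased by design. That goes too far. Deaths, MACE and the events in Appendix 2, including ventricular arrhythmia, left ventricular failure and myocardial ischemia, are captured whatever their causality. Echocardiography, Holter, ECG and laboratory tests are scheduled for everyone. Section 7.2.6.3 asks for all adverse events, and unblinding of investigators is an inference.

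It also stands that the consequence is limited. Assessment VI lies outside the formal study, the protocol states no 24-month hypothesis test, and quality of life is a secondary endpoint at month 6. Only MACE is listed in Section 3.2 without a time point, so the place of 24-month events in that endpoint is not settled.

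**Conclusion.** The concern holds as an inconsistency with a practical consequence. The protocol fixes an unblinding event for all patients but not its date relative to Assessment VI, and nothing preserves the blind until then. Under the formal closing rule, uniform accrual over 60 months and disclosure at the close, about 30% of patients (about 43 of 142) would know their arm before the 24-month visit. Late-loaded accrual raises this; delay between close and disclosure lowers it. It is 0% if 2.5 years runs from each operation. The counts use the planned 142 and ignore death and withdrawal; the share does not depend on the sample size.

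What is exposed is 24-month quality of life, reintervention reporting and, if sites also learn the allocation, relatedness judgements. The primary endpoint and the secondary endpoints with a stated month-6 time point are unaffected on any supported reading. The point is modest and cheap to remedy.

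**What to change.** Replace the unblinding sentence in Section 3.1 with a rule to this effect:

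*Apart from emergency, regulatory and Safety Monitoring Board unblinding under Sections 5.4 and 9.9, a patient and the treating site are told the allocation only after that patient's Assessment VI data have been entered. The decision on stored material is taken then. Opening the code for the 6-month analysis does not disclose it to sites or patients.*

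Two reconciliations belong with it:

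- Align the 2.5 years in Section 3.1 with Section 9.10, stating the starting point or removing the figure.
- Reconcile Sections 6.3.1.5 and 7.2.6.3 on which adverse events are documented after month 6.

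The cost is a few sentences in the protocol, and in the patient information where it repeats the rule. Samples from patients who have not reached month 24 at study close would be stored up to 18 months longer (84 − 66 for the last patient), and those patients would wait that much longer to decide on them.
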